# The Kusamala Program for primary caregivers of children 6–59 months of age hospitalized with severe acute malnutrition in Malawi: study protocol for a cluster-randomized controlled trial

**DOI:** 10.1186/s13063-017-2299-3

**Published:** 2017-11-17

**Keywords:** Severe acute malnutrition, Psychosocial stimulation, Nutrition, WASH, Child development, RCT

## Abstract

**Background:**

Severe acute malnutrition (SAM) is associated with high mortality rates and impairments in growth and development in children that do survive. There are complex nutritional, health, and behavioural risk factors involving severely malnourished children and their primary caregivers, requiring integrated intervention approaches.

**Methods:**

A cluster-randomized controlled trial at the Queen Elizabeth Central Hospital in Blantyre, Malawi will be conducted to evaluate the effectiveness of a 4-day hospital-based intervention programme directed at primary caregivers. This programme, titled the Kusamala Program, aims to improve developmental and nutritional outcomes in children with SAM. Up to six primary caregivers and their children will be enrolled to groups each week, which will be randomly allocated to intervention or comparison arms. The intervention package consists of interactive counselling on three modules: 1) nutrition and feeding; 2) water, sanitation, and hygiene (WASH); and 3) psychosocial stimulation. Data collection will be performed at enrolment, at discharge from hospital, and at 6 months following discharge. The primary outcome is child development assessed with the Malawi Developmental Assessment Tool (MDAT), a validated measure of gross and fine motor, language, and social development.

**Discussion:**

This intervention programme is unique because it utilizes primary caregivers’ time spent in-hospital while children receive treatment for SAM. The programme has the potential to be effective in addressing multiple aspects of child, nutrition and development.

**Trial registration:**

ClinicalTrials.gov, NCT03072433. Registered on 7 March 2017.

**Electronic supplementary material:**

The online version of this article (doi:10.1186/s13063-017-2299-3) contains supplementary material, which is available to authorized users.

## Background

### The global burden of malnutrition

Worldwide, malnutrition is a direct or indirect cause of an estimated 45% of all child deaths [1]. Severe acute malnutrition (SAM) is one type of malnutrition that manifests in two forms: marasmus, identified by severe wasting; and kwashiorkor, characterized by the presence of bilateral pitting oedema [2]. Morbidities such as pneumonia, human immunodeficiency virus (HIV), or diarrheal disease often complicate effective management of SAM and are associated with increased mortality [1, 3–5]. Children with SAM are often admitted to hospital due to serious illness rather than malnutrition alone. Mortality in hospitalized children with SAM can be up to 35% even when World Health Organization (WHO) protocols are followed [4, 5].

### SAM and child development

Although most children survive episodes of SAM, there are limited studies that have examined long-term outcomes of SAM such as child growth and development. Children with SAM are known to be susceptible to nutritional problems such as growth faltering, and are hypothesized to have poor motor and cognitive outcomes due to maturation of the brain being constrained in malnourished children [4, 6–9]. The implications of impaired child development are major at the individual level due to reduced intellectual and physical capacity. The most prominent study on development in children with SAM was performed in a small cohort by Grantham-McGregor et al. beginning in 1975 [9, 13]. Results of this study suggested that children with SAM have long-term developmental delay compared to non-malnourished children [9, 13]. This can ultimately translate to decreased national-level economic progress [10–12].

### In-patient treatment guidelines for SAM

In-patient hospital treatment is required for children with SAM that have: 1) severe bilateral pitting oedema; 2) severe wasting with any bilateral pitting oedema or medical complications; 3) medical complications with any bilateral pitting oedema; or 4) no appetite [2, 14, 24]. The duration of treatment is generally between 1 and 2 weeks. The WHO *Guidelines for the inpatient treatment of severely malnourished children* include instructions to provide an environment that is stimulating for children during their treatment and support for primary caregivers, as well as preparation for follow-up after discharge from hospital with basic instructions for care of children [15].

Despite the promotion of psychosocial stimulation by the WHO, a recently published systematic review clearly outlines the need for scientific evidence behind the provision of psychosocial stimulation for children with SAM to improve developmental and nutritional outcomes [13, 16]. Only two trials, one in Jamaica by Grantham-McGregor et al. described previously and a second in Bangladesh, examined the effects of stimulation activities for children during hospital treatment of SAM [9, 13, 17]. In the Jamaican study, children with SAM were enrolled to either an intervention group (*n* = 21), receiving psychosocial stimulation 6 days per week in hospital and continuing weekly then bi-weekly over 3 years after hospital discharge, or to a comparison group (*n* = 18) [9]. These children were compared to non-malnourished controls (*n* = 21) [9]. This study, as well as the Bangladesh study, reported that psychosocial stimulation could help to recover some of the deficits in development in children with SAM [9, 13, 17]. Some of the limitations of these studies were a small sample size and a high likelihood for selection, reporting, and attrition bias. In addition, the developmental tools used were not locally standardized and the types of interventions tested in both studies are unlikely to be feasible in most resource-constrained settings [9, 13, 17].

### Trial and intervention rationale

In order to justify the implementation of psychosocial interventions for children with SAM, further research is needed. Importantly, there is evidence that links nutritional factors, water, sanitation, and hygiene (WASH), and psychosocial stimulation to child development and nutritional status [12, 18–20]. Integrated interventions that unite these elements could be most effective in improving developmental and nutritional outcomes in children with SAM.

## Methods

The Standard Protocol Items Recommendations for International Trials 2013 Statement has been followed for the reporting of this protocol (see Additional file 1) and for reporting the timeline of the trial (Fig. 1) [21].

**Fig. 1 Fig1:**
[figure not shown]
Timeline of enrolment, intervention and comparison, and assessments

### Objectives and hypothesis

The primary objective of the trial is to evaluate the effects of a 4-day hospital-based intervention for primary caregivers of children with SAM on child development and nutritional status after 6 months.

The secondary objective is to understand the effects of this programme on knowledge, attitudes, and practices, as well as mental health status of primary caregivers.

The hypothesis is that the intervention programme for primary caregivers will improve developmental and nutritional outcomes in children hospitalized with SAM.

### Trial overview and design

This study will evaluate a comprehensive structured intervention package for primary caregivers of children aged 6 to 59 months hospitalized with SAM. It will be a pragmatic trial aimed at replicating how this type of intervention could be delivered in a real nutrition rehabilitation unit (NRU) setting and its effectiveness in this setting [22]. The primary outcome is child development, which will be assessed using the Malawi Developmental Assessment Tool (MDAT), a locally adapted and validated tool for evaluating multiple domains of child development (i.e. gross motor, fine motor, language, and social domains) [23].

The design of the study is a cluster-randomized controlled trial (superiority design) that will be conducted at the Moyo NRU of the Queen Elizabeth Central Hospital in Blantyre, Malawi (NCT03072433). A cluster-randomized controlled trial design was selected because the intervention is most feasible if delivered to groups of primary caregivers rather than individual caregivers. This design will also prevent temporal overlap between the two study arms: 1) an intervention arm of primary caregivers and children with SAM participating in an intervention programme; and 2) the comparison arm of primary caregivers and children with SAM receiving standard care. All other clinical and nutritional aspects of care will be equivalent; children will be treated per hospital protocol and WHO guidelines [24]. One day of each week will be used to recruit and enrol an estimated average of four primary caregiver-child pairs. Once formed, the group will be randomly assigned to either the intervention or comparison arm. Recruitment and enrolment will not overlap with the delivery of intervention sessions, although it is possible that children from different groups will be in the NRU at the same time depending on the duration of their in-patient treatment.

An internal pilot study (exploratory design) will be conducted within the full randomized trial and will reflect the design of the full trial [25, 26]. The internal pilot study will include at least the first 15 primary caregiver-child pairs recruited to each arm, for a minimum of 30 primary caregiver-child pairs [25, 26]. As there are few previous trials evaluating long-term development in children with SAM, this internal pilot study will inform the design of the larger randomized control trial by estimating the variance of MDAT scores. This will allow for a more accurate sample size calculation. The internal pilot study will also establish the adherence and engagement rates of participants to the intervention [25].

### Participant recruitment and enrolment

Children admitted to hospital with complicated SAM and their primary caregivers will be recruited at the NRU after being screened for eligibility within 3 days of admission to the NRU (*–t*
_*1*_). It is estimated based on hospital records from the NRU that there will be sufficient SAM admissions to recruit primary caregivers and children to each group.

Prior to seeking informed consent, information about benefits and risks of this study will be provided verbally and on an information sheet in Chichewa to the primary caregivers of children admitted to hospital. Written informed consent will be requested of the primary caregivers on behalf of themselves and their children (*–t*
_*1*_). For those unable to read or write, the information will be read to them in Chichewa. In these cases, informed consent by signature or thumbprint will be observed by an impartial witness.

### Identification of SAM in children

Marasmus or severe wasting, defined by weight-for-length *z* scores (WLZ) or weight-for-height *z* scores (WHZ) of at least three standard deviations (SD) below the median *or* by a mid-upper arm circumference (MUAC) of less than 115 mm; and/orKwashiorkor, defined by nutritionally-induced bilateral pitting oedema.

### Inclusion criteria

Child between 6 and 59 months with SAM;Child admitted to hospital because of SAM with medical complications as defined by the current WHO guidelines or who has no appetite if there are no complications [2, 15];Primary caregiver (self-identified) present at hospital.

### Exclusion criteria

Primary caregiver declined to give informed consent;Child with a known terminal illness (i.e. in the opinion of the treating physician the child is likely to die within 6 months);Child requires a surgical procedure.

This study will not exclude children with cerebral palsy and other types of neurodisability as they represent a significant portion of admitted children with SAM and could benefit from the intervention.

### Intervention: the Kusamala Program

The Kusamala Program is a 4-day counselling programme, led by NRU nurses, for primary caregivers of children with SAM in an NRU setting. Kusamala means “to take care” in Chichewa. The programme incorporates multiple modules aimed at addressing the diverse causes and consequences of SAM. The modules include:Nutrition and feeding: breastfeeding, complementary foods available in the country, safe food preparation, prevention, and early identification of malnutrition;WASH: handwashing of caregivers and children’s hands with soap after defecation and before preparing food and feeding; andPsychosocial stimulation: to promote sensitive and responsive parenting and to identify activities that the primary caregiver and child can do together, including speaking or singing, playing with toys, and looking at pictures and books.

Each of the 4 days (*t*
_*1*_
*–t*
_*4*_) of the Kusamala Program involves 45 min of counselling performed in the back bay of the NRU, which is separated from the rest of the ward by a wall. The first three sessions cover each of the three modules (i.e. one module per session), whereas the final day is a summary of all modules.

Materials for the first two modules of the Kusamala Program were based on adaptable nutrition and WASH communication and support materials from the United Nations Children's Fund (UNICEF) [27, 28]. Nutritional messages and materials for children above 2 years of age have been added since these UNICEF materials focus on infants and young children. Furthermore, there will be an additional emphasis on prevention and early identification of malnutrition.

For the psychosocial stimulation module on the third day of the intervention, the WHO Care for Child Development Package will be used to promote sensitive and responsive caregiving for age- or ability-appropriate play and communication activities [29]. Psychosocial stimulation is an integral component of the Kusamala Program. For this reason, primary caregivers and their children are also involved in 45 min of supervised and interactive play on each of the 4 days after the counselling sessions. A basket of play items is available in the NRU for children and primary caregivers to use during the play sessions. There are traditional Malawian toys, including small drums, rattles, and shakers, in addition to “Western” toys, such as colourful stacking blocks. Primary caregivers can also make their own toys such as shakers by adding beans or bottle caps to empty plastic jars available in the basket. Nurses supervise these sessions and actively encourage primary caregivers to engage in play and communication activities appropriate for the age and stage of development of their children.

Four behaviour change techniques including information, materials, media, and performance have been integrated into the Kusamala Program. Results from 24 studies to improve health and nutritional outcomes showed that effect sizes on outcomes were higher when three or four techniques were applied [30]. Firstly, nurses use a flipbook with coloured images to provide information to participants [30]. Primary caregivers will be given: two take-home images of nutrition and WASH messages, respectively (i.e. media); a toy that is appropriate for their child’s stage of development (i.e. materials); and a certificate of completion of the Kusamala Program [30]. During the intervention sessions, nurses also involve primary caregivers in practicing relevant activities including feeding, handwashing, and play (i.e. performance) [30].

### Comparison: the standard of care and unsupervised play sessions

Participants in the comparison group will receive the standard care at the NRU including clinical stabilization and nutritional rehabilitation. Besides this, nurses will instruct primary caregivers to take their children to the area of the NRU where play items will be available for use during their hospital stay. However, nurses will not be involved in the same interactive psychosocial stimulation sessions in which participants in the intervention groups partake. Participants will not be counselled about the importance of play; primary caregivers will not be advised which toys are appropriate and the play sessions will not be supervised. Having primary caregivers and children go to the back bay also acts as a method of blinding study personnel and participants so they are unaware of the allocation.

At the time of discharge from the NRU, nurses counsel primary caregivers on nutrition and WASH for an estimated 15 min. Nurses have been trained on nutrition and WASH messages to discuss with participants at discharge, yet this counselling does not follow a strict protocol.

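### Both arms use the back bay, stays can run across weekly groups, and no stated rule keeps comparison families out while Kusamala sessions run

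*Protocol article*

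**What the plan says.** Four parts of the protocol article bear on this.

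- **Intervention: the Kusamala Program.** Each of the four days has "45 min of counselling performed in the back bay of the NRU, which is separated from the rest of the ward by a wall". A further 45 minutes of supervised play follows the counselling each day. The wall is the only physical separation that the article describes.
- **Comparison: the standard of care and unsupervised play sessions.** Nurses tell comparison caregivers to "take their children to the area of the NRU where play items will be available for use during their hospital stay". The section then identifies the place and gives a reason for using it: "Having primary caregivers and children go to the back bay also acts as a method of blinding study personnel and participants". It also says what this arm must not receive: "Participants will not be counselled about the importance of play; primary caregivers will not be advised which toys are appropriate".
- **Trial overview and design.** On the cluster design it says: "This design will also prevent temporal overlap between the two study arms". On the weekly cycle: "One day of each week will be used to recruit and enrol an estimated average of four primary caregiver-child pairs". Later in the same paragraph it concedes that "it is possible that children from different groups will be in the NRU at the same time depending on the duration of their in-patient treatment".
- **In-patient treatment guidelines for SAM.** On length of stay: "The duration of treatment is generally between 1 and 2 weeks".

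**The concern.** The wall keeps Kusamala sessions away from the ward, but comparison families are sent to the same side of it. The only time frame attached to their use of the play items is the hospital stay. It is not tied to their own group's four days.

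Within its own week a comparison group has no newly formed intervention group beside it. The difficulty comes later, when a comparison family is still admitted and the next group is an intervention group. That family has been told to use a room where nurses are now counselling from a flipbook, encouraging play and having caregivers practise feeding, handwashing and play. Much of this can be seen or overheard, and the play counselling, toy advice and supervision are what the comparison arm is meant not to receive.

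Anything absorbed this way makes the arms more alike and moves the estimated difference in MDAT *z* scores at 6 months toward zero. Without some record of exposure, a null result would be harder to interpret.

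**Working it through.** **1. Can the arms meet in the room?**

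- Same room: yes. Counselling is in the back bay, and the comparison section sends its families there.
- Same time on the ward: possible. Groups form every week and treatment generally lasts 1 to 2 weeks. The design section concedes that groups may be in the NRU together.
- Rule separating their use of the room: none is stated. The article also does not say that comparison families are present during sessions.

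**2. How often could a later group be an intervention group?** The allocation ratio is not stated, so assume independent 1:1 weekly allocation. For a comparison family still admitted during the sessions of *k* later groups, the chance that at least one is an intervention group is 1 − 0.5^*k*.

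- *k* = 0: 0
- *k* = 1: 0.50
- *k* = 2: 1 − 0.25 = 0.75

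This is the chance of an opportunity, not of exposure. The family must also enter the room during one of the two 45-minute blocks.

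**3. Reproduce the planned sample size.** Inputs from the sample size section: α = 0.05 (taken as two-sided), 80% power, 1.6 used as the SD, 0.5 used as a difference in *z* score, and ICC 0.001.

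- *n* per arm = 2 × [1.6 × (1.960 + 0.842) / 0.5]² = 160.7
- Design effect at an average of four pairs per group = 1 + (4 − 1) × 0.001 = 1.003
- 160.7 × 1.003 = 161.2

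This agrees with the stated 160 per arm. Reading 0.5 as a true Cohen's *d* gives 63 per arm, and reading 1.6 as a variance gives 101. The stated figure therefore rests on the reading used here.

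**4. Illustrate the dilution.** Let *c* be the share of comparison families exposed and *f* the share of the effect that they gain. The article gives neither. Take *f* = 0.5. The diluted difference is 0.5 × (1 − *c* × *f*). Power is for a two-sided *t*-test with 160 per arm and SD 1.6; the design effect of 1.003 is ignored as negligible.

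| *c* | Difference (*z*) | Power | *n* per arm for 80% |
|---|---|---|---|
| 0 | 0.500 | 79.6% | 162 |
| 0.10 | 0.475 | 75.4% | 180 |
| 0.25 | 0.4375 | 68.4% | 211 |
| 0.50 | 0.375 | 55.2% | 287 |

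**5. What these shares require.** If a stay can meet only one later group, *c* = 0.5 × (share of families who stay on and would be exposed if that group were an intervention group). So *c* = 0.10 needs that share to be 20%, *c* = 0.25 needs 50%, and *c* = 0.50 needs 100%. The last row is an extreme case.

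**The case against.** A reader might infer that comparison families are placed beside the intervention for their whole stay. The text does not say that. It says that play items are available during the stay, it speaks of play sessions, and it gives no frequency or duration of back-bay use. Co-presence needs three things together: a stay that runs into a later week, an intervention group in that week, and entry during a session. The Discussion says that four days match the average minimum in-patient stay, so some families may leave before the next group's sessions start.

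Other points on that side:

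- **The possible overlap of groups is disclosed.** This is true, and the present point depends on it. But the disclosure does not deal with the shared room.
- **A room timetable is operational detail that an article may leave out.** This is fair for a timetable as such. Here, however, the article does describe the room arrangement and presents shared use as an advantage for blinding, so the consequence of that stated rule can be examined. Assessments held privately in the back bay when it is available suggest some management of the room, but not a rule for session times.
- **Comparison use of the room may be recorded.** Table 1 lists attendance measures only for the Kusamala Program, but it lists outcomes. It does not show that comparison use goes unrecorded.
- **The dilution rates are assumed, and half the effect may be generous.** This stands. Overhearing would not supply the take-home images, the toy or the coached practice.
- **A null result would not be wholly uninterpretable.** This also stands. Caregiver knowledge and practices and the HOME Inventory at 6 months give indirect evidence on whether the arms separated.
- **Separate hours could reveal allocation.** This stands, and it shapes the fix.

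**Conclusion.** The point holds in a limited form. The plan sends both arms to the back bay, admits that groups can overlap, and states no rule that keeps an earlier comparison group out while a later intervention group's sessions run. The statement that the design prevents temporal overlap cannot be relied on for this. It is true of recruitment and of a group's own week, but not of families who stay longer. Any resulting exposure would bias the primary comparison toward no effect.

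The size is unknown. With half the effect gained by 10% to 25% of comparison families, power falls from about 80% to between about 75% and 68%. These figures rest on assumed exposure shares, two-sided α, SD 1.6 and a true difference of 0.5 *z*. The planned size has no reserve, so even modest dilution takes power below 80%. The documents do not show that exposure will occur, only that following the plan as written allows it. Because the remedy is nearly free and protects the primary comparison, it should be made.

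**What to change.** In the comparison section, replace open use of the play items during the stay with a room-use rule:

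1. In its own study week, each comparison group has its unsupervised play in the same daily back-bay slot that an intervention group would occupy. Attendance then looks the same in both arms from outside the room, which keeps the blinding device.
2. In later weeks, families still admitted may use the back bay only outside the current group's two 45-minute sessions. Only the current week's group is then in the room during them.
3. Comparison families' use of the back bay is recorded, so that any exposure can be reported by arm.

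In the design section, reword the overlap claim to say that recruitment and each group's own sessions do not overlap between arms, that stays may, and that the room-use rule covers those stays.

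The cost is a short timetable, a small amount of extra recording, and slightly less free access to the toys for families who stay into a later week. On a session day the restriction is 2 × 45 = 90 minutes. No extra participants are needed.

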### Implementation outcomes

Participant engagement and adherence to the Kusamala Program will be evaluated based on the proportion of participants that attend the first day of the programme (*t*
_*1*_) and the number of participants that attend all 4 days of the programme (*t*
_*1*_–*t*
_*4*_), respectively. Fidelity of 20% of the intervention sessions will be assessed using a tool designed to capture duration of sessions, delivery of specific intervention content, and counselling skills according to the WHO Care for Child Development Package [29]. Following the intervention, knowledge and attitudes of primary caregivers who participate in the Kusamala Program will be demonstrated with the use of a questionnaire at discharge from hospital and at follow-up.

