### Biostatistics procedure and blinding

A biostatistician (CB) completed the computer-generated random allocation sequence for each study week and placed the sequence in sealed envelopes to be opened at the start of each week by a nurse at the NRU. NRU staff (apart from NRU nurses) and those doing screening, recruitment, enrolment, and data collection will be blinded. There are no expected reasons for un-blinding of study team members to occur. Blinding of the analysis will be performed by a biostatistician with the use of a dummy variable to code for each group. A data monitoring committee will not be necessary to analyse results un-blinded during the trial because the intervention is of very low risk. Nonetheless, an interim analysis will be completed with the internal pilot study data.

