### Data collection and management

Data collection will be performed by three different enumerators who have been trained on all relevant assessment tools and questionnaires, including the MDAT. Baseline data collection will take place over approximately 80-week-long cycles, depending on enrolment rates, with assessments performed at enrolment (–*t*
_*1*_) and at discharge (*t*
_*5*_). These data collections will be done privately in the NRU, either in the procedures room or in the back bay depending on availability of these locations. Home visits will be conducted for follow-up assessments 6 months after children are discharged from hospital (*t*
_*6*_) over the course of 80 weeks. For participants who prefer not to be visited in the home, they will be asked to come back to the NRU for follow-up assessments.

Investigators will maintain medical and research records for this trial in compliance with regulatory and institutional requirements for the protection of confidentiality of subjects. All personnel with access to data and information related to this trial will take all reasonable precautions to maintain the confidentiality of information. Data will be collected using paper forms which will be kept in a locked filing cabinet and will be accessed only by the investigators. Data entry will be performed into a Research Electronic Data Capture database, which includes automated checks for data values with coded numbers [41]. De-identified data will be exported in a password-encrypted file.

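### The protocol claims participant blinding that its design cannot deliver, and assessor blinding of the 6-month MDAT is at risk

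*Protocol article*

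**What the plan says.** The protocol article makes two statements about blinding.

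- *Comparison: the standard of care and unsupervised play sessions* says that having comparison families go to the back bay "also acts as a method of blinding study personnel and participants so they are unaware of the allocation".
- *Biostatistics procedure and blinding* exempts the unit's nurses but says that "those doing screening, recruitment, enrolment, and data collection will be blinded". It adds: "There are no expected reasons for un-blinding of study team members to occur".

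Other sections describe what each arm receives and how outcomes are collected.

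- *Intervention: the Kusamala Program* sets out four days, each with 45 minutes of counselling and 45 minutes of supervised play. Caregivers are given "two take-home images of nutrition and WASH messages", "a toy that is appropriate for their child" (suited to the child's developmental stage) "and a certificate of completion of the Kusamala Program".
- The comparison section lists standard care, unsupervised access to play items and about 15 minutes of nutrition and WASH counselling at discharge. It lists no take-home items.
- *Data collection and management*: "Home visits will be conducted for follow-up assessments 6 months after children are discharged from hospital". Families who prefer it may come to the unit instead. Three enumerators, trained on all the tools including the MDAT, collect the data.
- *Secondary outcomes* places the HOME Inventory, which includes observation, at the same 6-month time point.
- *Implementation outcomes*: "knowledge and attitudes of primary caregivers who participate in the Kusamala Program will be demonstrated with the use of a questionnaire at discharge from hospital". The same sentence also names follow-up. Table 1 lists the discharge version as an implementation outcome on intervention content.

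**The concern.** The blinding statements do not fit the rest of the design. A caregiver who has been through four days of sessions and holds a certificate naming the programme cannot be unaware of having received it. The enumerator who scores the primary outcome usually does so in that caregiver's home, where the items may be visible or the sessions may come up in conversation.

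Two things are at stake. The MDAT is scored pass or fail by an assessor, so knowledge of the arm could influence borderline items; the expected direction is towards the intervention, though that is not certain. In addition, the final report would carry a blinding claim that the trial cannot support, and readers would judge the risk of bias in the primary outcome on a wrong premise.

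**Working it through.** **Step 1. Participants.** Set side by side what each arm experiences.

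| Feature | Intervention | Comparison |
|---|---|---|
| Use of back bay | yes | yes |
| Nurse counselling sessions | 4 days × 45 min | none during the stay |
| Play | 4 days × 45 min, supervised and coached | unsupervised, no advice |
| Discharge counselling on nutrition and WASH | not described separately | about 15 min |
| Images, toy, certificate | listed | not listed |

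Only the first row is the same. *Trial overview and design* also allows children from different groups to be on the unit together, so caregivers can compare experiences. Participant blinding is not achieved.

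**Step 2. Assessors at 6 months.** The primary outcome is the MDAT at this time point. The default setting is the home, and the HOME Inventory requires the home environment to be observed. The certificate identifies the arm outright; the images and toy are weaker signs. Exposure is plausible but not certain.

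**Step 3. Assessors at discharge.** The MDAT is also done at discharge. The discharge questionnaire is described only for caregivers who take part in the programme. If only one arm receives it, an enumerator who administers it learns the arm at the time point of that MDAT. If both arms receive it, this route disappears. The text does not settle which.

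**Step 4. Scale of the possible effect.** The document gives no figure for assessor bias, so the bias below is assumed. The other inputs are from *Sample size calculation*: SD 1.6, difference 0.5, α = 0.05 (taken as two-sided), power 80%, intracluster correlation 0.001. The average group size of 4 is from *Trial overview and design*.

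The plan's own figure comes first, with 0.5 read as a raw z-score difference:

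- n per arm = 2 × [1.6 × (1.960 + 0.842) / 0.5]² = 160.7, rounded up to 161
- design effect = 1 + (4 − 1) × 0.001 = 1.003, giving 161.2, rounded up to 162

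The stated 160 per arm is reproduced closely enough to use. Then:

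- SE of the difference = 1.6 × √(2/160) = 0.179 (the design effect of 1.003 is negligible here)
- with no true effect and a scoring bias b, error rate = P(Z > 1.96 − b/SE) + P(Z < −1.96 − b/SE)

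| Assumed bias b (z) | b/SE | Two-sided error rate |
|---|---|---|
| 0.05 | 0.28 | 5.9% |
| 0.1 | 0.56 | 8.6% |
| 0.2 | 1.12 | 20% |
| 0.3 | 1.68 | 39% |

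The spread shows that the result depends on the assumption. It indicates sensitivity and does not estimate what happens in this trial.

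**The case against.** A reader might infer that home-visiting assessors will certainly see the items and so be un-blinded. The document does not support that. Families may choose to attend the unit, the visit comes six months after discharge, and nothing says the items are kept or displayed. A toy is weak evidence, since the programme's own play items are ordinary drums, rattles, shakers and blocks. That comparison families receive none of the items is inferred from their absence in that section; no sentence excludes it.

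A reader might also infer that correct answers on the 6-month knowledge questionnaire give the arm away. They are poor evidence: nurses counsel comparison caregivers on nutrition and WASH at discharge, and the questionnaire is a caregiver outcome for the whole trial.

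Nor does the document show that the discharge questionnaire is withheld from the comparison arm, who administers it, or that the same enumerator sees a given child at discharge and at six months. Those points remain conditional. The MDAT has been evaluated locally, and its items turn on whether the child can complete a task, which limits the room for judgement without removing it.

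Finally, visit order and masking instructions may sit in an operating manual that a condensed article omits. Their absence is therefore not the criticism. The criticism is that the article positively asserts participant blinding and expects no un-blinding while describing features that contradict the former and threaten the latter. That part stands.

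**Conclusion.** The concern holds in two parts of different strength. The claim that participants are blinded is wrong on the document's own description of the arms. The claim that data collectors are blinded is not disproved, but it is insecure, and the expectation of no un-blinding is too confident given home visits, home observation at the same time point and a possibly one-arm discharge questionnaire.

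The size of any bias cannot be derived from the document. The range of about 6% to 39% for the error rate rests on assumed scoring biases of 0.05 to 0.3 z, SD 1.6, 160 per arm and a two-sided test. The trial remains usable; the blinding statements need correcting, and simple safeguards for the primary outcome are worth adding.

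**What to change.** 1. At six months, complete and score the MDAT before the HOME Inventory and the knowledge questionnaire. Ask caregivers in both arms not to discuss hospital sessions beforehand.
2. Give the discharge knowledge questionnaire to both arms, after the discharge MDAT.
3. Have the enumerator record a guess of the arm straight after the MDAT, and report the guesses by arm. A guess may partly reflect how well the child performed, so read it with that in mind.
4. Delete the statement that participants are blinded and describe assessor blinding as attempted. Reconcile the comparison and blinding sections with those on the intervention, secondary outcomes, implementation outcomes and data collection.

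Do not ask families to put programme items away. The HOME Inventory observes the child's home environment, so hiding a toy would distort that outcome, and the request would tell comparison families that a programme exists.

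The cost is a short extra questionnaire in the comparison arm and one form item, with no extra staff. Recruitment began in November 2016, so families assessed before and after the change, including those in the internal pilot, would follow slightly different procedures. Changes to the 6-month visit affect both arms alike; any questionnaire added at discharge is new only for the comparison arm. The HOME Inventory and knowledge outcomes remain open to un-blinding, and this should be stated as a limitation.
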